##### Innovative procedure

*Innovative Medical Device (IMD): SinnoTest® Software version 2.0*

SinnoTest® is a therapeutic guidance device for patients suffering from chronic inflammatory rheumatism, in particular RA. SinnoTest® consists of the following three elements: “routine” biological assay of biomarkers from a blood sample, calculation algorithm, and graphical user interface (software and online application). This device was designed by the company Sinnovial. The assessment of its conformity was carried out by SurgiQual Institute.

Biomarkers are detected and quantified in blood samples of patients, using commercial tests aimed at determining the levels of these molecules. These results are sent to the SinnoTest® secure server. These data are processed by algorithms to determine the probability of response to the treatments available in the therapeutic arsenal (biological therapies). These algorithms were developed in a population of patients with a previous failure to iTNFs receiving the specific medication the algorithm was designed for. This data is sent to a secure server. The graphical user interface is an independent software, accessible through a web platform, which allows authorized health professionals to access the results of the analysis of individual patients. SinnoTest® is a stand-alone IMD-MD software, accessible via a web platform. Rheumatologists from the different centers will be contacted by email to register for the SinnoTest® online platform. A link in this email will provide access to the registration part of the application. The rheumatologists will then be able to connect to the SinnoTest® platform thanks to their personal identifiers.

*Process of the innovative procedure*

The selection of the bio-drug is carried out based on the recommendations of SinnoTest®. This test categorizes bDMARD based on the probability of response. It will allow to prescribe both original molecules and biosimilars in an equivalent way. In the SinnoTest® arm, the investigator prescribes the treatment defined as the most effective by SinnoTest®, except in case of contraindication. If contraindicated, the investigator prescribes the second-choice treatment (if any) of SinnoTest® in terms of efficacy.

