##### Reference procedure

There is currently no evidence of treatment response in RA. The choice of the treatment by the rheumatologist is therefore empirical. In order to simplify the process and favoring blinding, regardless of which arm the patient is randomized to, the usual rheumatologist will record two treatment proposals in the clinical history. On the one hand is the treatment that he would prescribe if the patient was randomized to the control arm and, on the other hand, the one that he would prescribe if the patient was randomized to the intervention arm and if SinnoTest® did not recommend any treatment (therefore, the proposed treatment in this case cannot be any of the 3 potentially recommended by SinnoTest®).

At the successive visit after 6–10 days in which the bDMARD will be prescribed, if the patient was randomized to the control arm, or was randomized into an intervention group, but SinnoTest® did not recommend any bDMARD, the medication previously registered by the usual rheumatologist will be used.

*Process of the reference procedure*

This is the current management of patients with RA, based on the EULAR recommendations. In case of rotation of biotherapy after prescription of a first biotherapy, the rheumatologist may prescribe the following bDMARDs: etanercept, adalimumab, infliximab, certolizumab, tocilizumab, abatacept, anakinra, golimumab, rituximab. All these bDMARDS can be prescribed as well as their biosimilars. In case of remission of more than 6 months, a reduction (dosage or spacing of the catch) of the biotherapy can be considered.

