### Participant timeline {13}

This study will be conducted by rheumatologists who have the opportunity to follow patients with RA and to conduct this study in good conditions and in accordance with regulatory and legal recommendations. The only difference in follow-up between the 2 groups is the addition of the “SinnoTest® Protein Biomarker” assay and the use of the results of this assay for therapeutic management.

Patients will be seen as part of their follow-up consultation in the Rheumatology department:
-Screening: verification of the eligibility criteria.-Inclusion or M0 visit: after information and signature of informed consent. All patients will have a SinnoTest® blood sample. At the end of this visit, the patient is randomized to the SinnoTest® group or the control group. In the control group, the SinnoTest® sample is kept but not analyzed.-6–10 days after the consultation, the prescription of the biotherapy recommended by the rheumatologist is sent by post. This prescription uses SinnoTest® results in the SinnoTest® arm.-Followed quarterly: M3 and M6.

As part of the proteomics substudy, for those patients who agree to participate, blood samples will be collected from the 2 groups in the M0 and in the M6 to study the variations in the proteomic profile of the patients. In addition, the remaining samples will be deposited in a biobank (in the recruitment center and in the Biobank of the Center Hospitalier Universitaire Grenoble Alpes, France). The participant timeline is presented in Table 1.

**Table 1 Tab1:** Schedule of enrollment, interventions, and assessments

Visits	Selection	Inclusion^a^ M0	M3 ± 2 weeks	M6 ± 2 weeks	M12 ± 2 weeks
Information^a^	✓				
Information and consent^b^		✓			
Confirmation of eligibility		✓			
Clinical/physical examination, rheumatoid arthritis		✓	✓	✓	
Routine blood analysis		✓	✓	✓	
Questionnaire EQ5D		✓	✓	✓	
Questionnaire HAQ		✓	✓	✓	
Biomarkers^c^		✓			
Patient booklet^d^		✓	✓	✓	✓
Administration/dispensation of biotherapy^e^		✓			
Biobank^f^		✓		✓	
Concomitant treatments		Collection throughout the study			
Adverse effects collection		Collection throughout the study			

^a^ Inclusion: The inclusion visit should be done in 2–3 weeks

^b^ Information and informed consent: The patient will sign informed consent for the main study and additional consent (optional) if they accept 6-month and 1-year inclusion samples, which will be retained for the creation of biobank

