#### Secondary outcome measures

##### *Clinical secondary outcome measures*

Disease activity, quality of life and disability

Clinical parameters at 6 months will be described using number of analyzed data, mean, standard deviation, Q1, Q3, minimum, maximum, and median, for DAS28-ESR, DAS28-CRP, EQ5D-5L, and HAQ.

Comparison between the study arms will be performed using linear regression models. All models will be adjusted by baseline variables, which will allow us to estimate an effect size for the difference between study arms regarding the clinical variables.

In addition, as disease activity, quality of life, and disability will be assessed at baseline, 3 months, and 6 months, their evolution will be analyzed using generalized estimating equations models nested by patient [26, 27] and adjusted by study visit and study arm, using a Gaussian family and Identity as link function. Different covariable structures will be tested (independent and exchangeable) and compared using the Quasi-Akaike Information Criterion [28]. Time × study arm interactions will assess different effects of time in the evolution of DAS28-ESR, DAS28-CRP, EQ5D-5L, and HAQ by study arm. A *p* value < 0.05 will be considered as a significant interaction. For each outcome, in case the interaction is not significant, we will consider that there is no statistically significant difference in the evolution of that outcome between study arms.

Software’s predictive model performance

Sensitivity, specificity, and positive and negative predictive values, and likelihood ratio will be described. The performance of the SinnoTest® will be calculated in the “SinnoTest®” arm by comparing the response predicted by the software and the response observed at 6 months. It will be analyzed globally and for each of the biotherapies.

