## Discussion

This single-blind controlled multicenter clinical trial study is the first validation study of a bDMARD response prediction software, bringing personalized medicine into the management of inflammatory rheumatism. This interest is also shared by pharmaceutical companies who wish to improve the stratification of patients and thus offer more targeted treatments.

We believe that the findings from this study will bring several benefits for the patient and for the health system as reducing patient exposure to ineffective and potentially poorly tolerated bDMARDs controls RA activity. The SinnoTest® will maximize the chances of successful treatment with biotherapy, the patient will benefit from the most appropriate treatment at the right time, which will improve its quality of life. In addition, it is important to consider the high proportion of patients receiving in clinical practice the bDMARDs which can be suggested by the SinnoTest® (up to 49% of the RA patients receiving a bDMARD [32]).

For public health, the short-term benefit will focus on optimizing the management of RA, improving and adjusting the SinnoTest® predictive software, thanks to the clinical results obtained. Data from clinical validation studies will be used to validate and improve the existing algorithm for performance, ergonomics, and functionality and anticipate access to the market by collecting medico-economic data and pursuing the search for partners to allow rapid deployment of the test in clinical practice. The SinnoTest® will allow the physician to optimize the selection of the biotherapy in real time.

The combination of SinnoTest® algorithms will optimize the selection of biotherapy for RA patients, and given the minimal risk for patients and the expected collective benefit, the benefit-risk ratio is very favorable.

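### Accuracy of SinnoTest is to be measured only in the arm where the prediction picks the drug, so sensitivity, specificity, NPV and likelihood ratios there reflect the design; only PPV and calibration are informative

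*Protocol article*

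**What the plan says.** The Objectives section gives, as the clinical secondary objective, a description of how the predictive model performs on new data from the trial. The statistical methods for that outcome state: "Sensitivity, specificity, and positive and negative predictive values, and likelihood ratio will be described". They fix the analysis set: "The performance of the SinnoTest® will be calculated in the “SinnoTest®” arm". The calculation is to be made "by comparing the response predicted by the software and the response observed at 6 months". They also fix the level of analysis: "It will be analyzed globally and for each of the biotherapies".

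Treatment in that arm follows the software. Under Innovative procedure, "the investigator prescribes the treatment defined as the most effective by SinnoTest®, except in case of contraindication"; a contraindication leads to the software's second choice, if there is one. SinnoTest covers adalimumab, rituximab and abatacept, and it may recommend none of them. For that case the Reference procedure says "the proposed treatment in this case cannot be any of the 3 potentially recommended by SinnoTest". The paragraph that closes Innovative procedure, however, gives a list for the same case that contains all three.

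Control patients are treated without the test. Their blood is drawn at M0, but "In the control group, the SinnoTest® sample is kept but not analyzed".

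**The concern.** Sensitivity and specificity need patients with a negative prediction for a drug who nevertheless take that drug, so that the prediction can be checked. In the SinnoTest arm the treatment rule removes almost all of them, because the software steers each patient to a drug it favours. This is verification bias by design: the outcome is seen mainly where the prediction is positive. The arm that could supply negative predictions is the control arm, where drug choice does not depend on the test, and its samples are not assayed.

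At stake is the reading of a trial that its Discussion presents as the first validation of this kind of software. Figures that would look the same for a good test and a useless one would be reported as properties of the device.

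**Working it through.** **The plan's own figure.** Sample size {14} gives 90 per group for 65% against 83.2%, two-sided 5%, power 80%. With pooled variance, n = [1.96·√(2 × 0.741 × 0.259) + 0.842·√(0.65 × 0.35 + 0.832 × 0.168)]² / 0.182² = 89.8, so 90. It reproduces and is not at issue. The article states no precision for the accuracy analysis.

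**Rules exactly as in Innovative procedure and Reference procedure.** Take a recommendation as a positive prediction. Suppose for illustration that all 90 are treated as recommended and 83.2% respond. Then TP = 90 × 0.832 ≈ 75, FP = 90 × 0.168 ≈ 15, FN = 0 and TN = 0.
- Sensitivity = 75/75 = 100%
- Specificity = 0/15 = 0%
- NPV = 0/0, undefined
- LR+ = 1/(1 − 0) = 1; LR− = 0/0, undefined
- PPV = 75/90 = 83%, about ±8 points (1.96·√(0.832 × 0.168/90) = 0.077)

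All but PPV come out the same whatever the true accuracy.

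**Some predicted non-responders get the drug anyway.** Let a fraction q of them receive it, and all predicted responders. Then
- observed Se = Se / [Se + q(1 − Se)]
- observed Sp = q·Sp / [q·Sp + (1 − Sp)]
- predicted negatives = 90·q·[0.65(1 − Se) + 0.35·Sp], using the planned 65% as base rate.

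The values of q, Se and Sp are assumptions.

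| True Se = Sp | q | Predicted negatives | Observed Se | Observed Sp |
|---|---|---|---|---|
| 0.9 | 0 | 0 | 1.00 | 0 |
| 0.9 | 0.05 | 1.7 | 0.99 | 0.31 |
| 0.9 | 0.10 | 3.4 | 0.99 | 0.47 |
| 0.8 | 0.10 | 3.7 | 0.98 | 0.29 |
| 0.7 | 0.05 | 2.0 | 0.98 | 0.10 |
| 0.7 | 0.10 | 4.0 | 0.96 | 0.19 |
| 0.5 | 0 | 0 | 1.00 | 0 |

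Likelihood ratios fail with them. At 0.8 and q = 0.10, LR+ = 0.976/(1 − 0.286) = 1.4 against a true 0.8/0.2 = 4. In this simple model NPV is not biased, but it rests on two to four patients.

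**Every no-recommendation patient gets a modelled drug**, which the list under Innovative procedure would allow. The article does not say how often nothing is recommended. Assume three independent predictions with Se = Sp = 0.8.
- Base rate 65%: P(negative) = 0.65 × 0.2 + 0.35 × 0.8 = 0.41, so 90 × 0.41³ = 6.2 patients. NPV is 0.28/0.41 = 0.683 and PPV is 0.52/0.59 = 0.881. This gives TN 4.2, FN 2.0, TP 73.9, FP 9.9; observed Se 0.97, Sp 0.30.
- Base rate 40%: P(negative) = 0.4 × 0.2 + 0.6 × 0.8 = 0.56, so 90 × 0.56³ = 15.8 patients. NPV is 0.48/0.56 = 0.857 and PPV is 0.32/0.44 = 0.727. This gives TN 13.5, FN 2.3, TP 54.0, FP 20.2; observed Se 0.96, Sp 0.40.

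Both remain far from 0.8.

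**What the control arm could add.** The Discussion puts the use of the three drugs at "up to 49% of the RA patients receiving a bDMARD". As a ceiling, 0.49 × 90 ≈ 44 control patients; 0.65 × 44 ≈ 29 responders and 0.35 × 44 ≈ 15 non-responders. For true Se = Sp of 0.7 to 0.9, about 17 to 19 would be predicted negatives. 95% half-widths (1.96·√[p(1 − p)/n]) are about ±11 to 17 points for sensitivity, ±15 to 23 for specificity and ±18 to 22 for NPV. Spread evenly over three drugs, 15 non-responders is about 5 per drug.

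**The case against.** **No cut-off is stated.** The article describes probabilities and a ranking. A first or second choice with a low probability could count as a predicted non-response. That stands as a caveat. But a test that can decline to recommend anything implies some threshold, and treating by rank still selects on the predictor.

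**The fallback rule is contradictory.** One list admits the three modelled drugs, the other passage excludes them, so the predicted-negative row need not be empty. This also stands, and the two passages must be reconciled. The working shows that even full use of the wider list leaves the bias.

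**No recommendation could be scored as predicted non-response.** Under the Reference procedure those patients' outcomes arise on a drug for which the software made no prediction, so they do not test it.

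**It is a descriptive secondary outcome.** True: no test depends on it, and the response comparison is untouched.

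A reader might infer that the secondary objective fails altogether. The article asks only for a description of performance, and PPV still gives part of that. A reader might also take the Discussion to say that these accuracy figures will be used to revise the algorithm. It speaks of validation data generally and does not name sensitivity, specificity or NPV.

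**Conclusion.** The point holds as a fault in the chosen analysis set. Calculated in the SinnoTest arm, sensitivity is driven toward 100%, specificity toward 0% and LR+ toward 1, while NPV and LR− are undefined or rest on very few patients. Exactly 100% and 0% apply only if no predicted non-responder receives the drug. A few exceptions move the figures but do not make them estimates of accuracy: specificity of 0.10 to 0.47 against a true 0.7 to 0.9 in the 5 to 10% scenarios. PPV, and calibration among treated patients, remain informative.

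The conclusion assumes that a recommendation is a positive prediction. The scenario sizes also rest on assumed accuracy, base rates and independence between drugs. The primary outcome is unaffected, and the secondary objective is partly met.

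**What to change.** **Core change, wording only.** In the SinnoTest arm, report PPV and calibration of the predicted probability for the drug actually received. Withdraw sensitivity, specificity, NPV and likelihood ratios there. State the cut-off that makes a prediction positive, and reconcile the two passages on what may be prescribed when nothing is recommended.

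**Optional addition.** After follow-up, assay the stored M0 samples of control patients who received adalimumab, rituximab or abatacept, withhold the results from clinicians, and estimate the withdrawn measures overall in those patients. This is more than a wording change:
- Participant timeline {13} and Implementation {16c} both say that the control sample is not analysed, so a protocol amendment and ethics review are needed.
- Consent must be checked; the separate consent in {26b} concerns the proteomics substudy and storage.
- Sample availability must be confirmed, because footnote c of Table 1 mentions biomarker sampling only for the intervention arm, against {13} and {16c}.

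The yield is limited. About 44 patients and 15 non-responders is a ceiling, taken from an upper figure for RA patients on bDMARDs in general. Section {11b} lists non-response at M3 as a reason to discontinue and says that such patients are not followed up, so fewer non-responders may have an observed M6 response. The estimates would be imprecise overall and not useful per drug. The extra cost is routine commercial assays on at most about 44 samples, with no added visits.

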##### *Pharmacoeconomic secondary outcome measures*

Incremental cost utility ratio at 6 months

The statistical analysis will proceed as follows:

Calculating the 6-month incremental cost-utility ratio from the community perspective using the following parameters: difference of the averaged total cost per patient and difference in the average number of QALYs generated by the strategies on both study arms. The ratio will be expressed in cost per QALY earned, which represents the additional cost that will have to be spent to earn a healthy year of life.QALYs will be calculated from the answers provided by EQ5D-5L, based on a weighting system reflecting preferences on the health status of the general Spanish population (41). The EQ5D questionnaire will be filled in by the patient at the inclusion visit and then at M3 and M6. The QALYs will be calculated by the area under the curve assuming a linear evolution of the quality of life between the measurement times. The average number of QALYs will be calculated for each of the strategies under study.In case of missing data, multiple imputation techniques will be carried out, in addition to sensitivity analysis, with the objective of checking that the assumptions made in the imputation were correct, and checking whether the conclusions of the study are modified, or not, according to the analysis strategy adopted.Although subjects will be followed up to 12 months, ICER will only be calculated at 6 months: as pointed out, according to the EULAR recommendations for biotherapy management in rheumatoid arthritis [25], 6 months is the time to assess if the therapeutic objectives of the medication has been achieved (remission or at least low disease activity). Based on those recommendations, if the patient is still active, treatment should be modified.Sensitivity analysis: Deterministic sensitivity analysis: it allows to take into account the uncertainty on certain parameters that can influence the cost of the strategies. We will consider the best and worst scenarios. Taking into account the variability in direct cost associated with treatment in RA [29], we will consider a ± 20% cost increase/decrease. This analysis will take into account in particular the impact of the cost of SinnoTest®, the impact of a change in the cost of treatments through biotherapy, the impact of the cost of work stoppages and the time of the caregivers, and probabilistic sensitivity analysis: it will include the calculation of the confidence intervals of the cost-utility ratio by the nonparametric Bootstrap method and the plot of the associated acceptability curve.In addition to the cost-utility ratio, differences in cost and utility will be analyzed separately: Comparison of the cost of the two strategies: the difference in costs between the groups will be tested by a Student test or a nonparametric test (Mann-Whitney tests) in case of non-Gaussian distribution. The choice of the test will be made with regard to the distribution of costs in each group (Shapiro-Wilk test, on raw data or, if necessary, on transformed data. In addition, distribution will also be assessed using histograms). The construction of the average cost confidence interval will be based on the nonparametric Bootstrap method and comparison of the utility: The number of QALYs will be calculated taking into account the time elapsed between two successive measurements. If the initial utility level between the groups differs (> 10%), a comparison of the number of QALYs between the groups will be made from a linear model to adjust for this level of utility [30]. Given the time horizon, no updates will be made; those of the inclusion visit (M0) will be taken.Multivariable linear regression method will be used to determine the explanatory factors of the average cost per patient of the strategies (i.e., age, sex, socio-professional category). In a first step, bivariable analysis will be carried out. Those variables with a *p* value < 0.15, plus age and gender, will be included in the multivariable analysis. Different models will be compared using the Akaike Information Criteria.

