### Sample size {14}

To re-evaluate the metrological properties of SinnoTest®, including 90 patients per group will highlight a differential response rate between the software arm and the control arm of more than 18.2%, considering a current response rate of 65% (defined as an EULAR good response [24]) with conventional care (control arm). The number of subjects required was estimated considering a bilateral alpha risk at 5% and a power of 80%. In total, 180 patients will be the estimated number of participants needed to achieve study objectives.

Due to the subject’s and the study’s characteristics, no allowance for loss to follow-up was considered in the sample size calculation: patients with a chronic disease, probably being followed up in the same center and by the same rheumatologist for some time (> 1 year), and the short follow-up time for the primary outcome.

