
##### Incremental cost-effectiveness ratio at 6 months

The incremental cost-effectiveness ratio at 6 months will be calculated from the cost differential of the strategies and the efficiency differential defined by the rate of good responder patients in each group. The ICER and the 6 months will be subjected to a deterministic and probabilistic sensitivity analysis.

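### The planned bootstrap interval for the 6-month cost-utility ratio is likely to be hard to interpret, because the QALY difference will probably be small against its standard error; net monetary benefit avoids this from the same replicates

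*Protocol article*

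**What the plan says.** The statistical section on pharmacoeconomic secondary outcomes builds the cost-utility ratio from the "difference of the averaged total cost per patient and difference in the average number of QALYs generated by the strategies on both study arms". The horizon is fixed: "ICER will only be calculated at 6 months". EQ-5D is completed "at the inclusion visit and then at M3 and M6", and QALYs are "calculated by the area under the curve assuming a linear evolution of the quality of life between the measurement times".

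Under probabilistic sensitivity analysis the plan names two outputs: the "calculation of the confidence intervals of the cost-utility ratio by the nonparametric Bootstrap method" and "the plot of the associated acceptability curve". The same section also compares costs and QALYs between arms separately. The article states no willingness-to-pay value and no rule for replicates in which the QALY difference changes sign.

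The sample size section plans for "including 90 patients per group", based on the response rate and not on QALYs.

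**The concern.** A ratio is a poor scale for an interval when its denominator may be zero. If some bootstrap replicates have a positive QALY difference and others a negative one, the sign of the ratio no longer identifies the result. A negative value is either cheaper and better (dominant) or dearer and worse (dominated). A positive value is either dearer and better or cheaper and worse. The ratio also passes through infinity as the denominator crosses zero. Sorting such values to obtain interval limits places opposite conclusions next to each other.

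The design makes this plausible. Over 6 months no patient can accrue more than 0.5 QALY, and even the full design effect changes response status in fewer than one patient in five. At stake is whether the interval reported beside the cost-utility ratio can be read at all.

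**Working it through.** **1. The plan's own figure.** For 65% against 83.2%, two-sided alpha 5% and power 80%, the pooled-variance formula for two proportions gives n = [1.960·√(2·0.741·0.259) + 0.842·√(0.65·0.35 + 0.832·0.168)]² / 0.182² ≈ 89.8. That is 90 per arm, with power 80.1%, so the stated sample size reproduces.

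**2. Inputs.** From the article: 90 per arm, an 18.2-point response difference, EQ-5D at M0, M3 and M6, and linear area under the curve. Assumed, because the article gives none: a responder-minus-non-responder utility gain of 0.10 to 0.20, an SD of 6-month QALYs of 0.06 to 0.12, and a utility difference between arms that arises only through response, grows linearly to M3 and then stays level.

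**3. Expected QALY difference.** If the arms differ in utility by d at M3 and M6, the area is 0.25·d/2 + 0.25·d = 0.375·d, with d = 0.182 × gain.
- Gain 0.10: 0.182 × 0.10 × 0.375 = 0.0068
- Gain 0.15: 0.0102
- Gain 0.20: 0.0137

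**4. Standard error.** SE = SD·√(2/90) = 0.149·SD. This is 0.009 for SD 0.06 and 0.018 for SD 0.12.

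**5. Chance of a negative denominator.** P = Φ(−difference/SE).
- Most favourable corner (gain 0.20, SD 0.06): z = 1.53, P = 6%
- Least favourable corner (gain 0.10, SD 0.12): z = 0.38, P = 35%

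This is also the approximate share of negative replicates in a trial that observes exactly the expected difference. In a simulation over these assumptions (cost difference 500 euros, cost SD 3,000 euros, both assumed), 65% to 94% of trials had more than 2.5% of replicates with a negative denominator.

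**6. Wider ranges.** With a gain of 0.05 to 0.30, SD 0.04 to 0.125, and either half or all of the M6 difference present at M3, the QALY difference is 0.002 to 0.020 and the SE 0.006 to 0.019. In 55 of 60 combinations more than 2.5% of replicates are expected to be negative. The five exceptions combine a gain of 0.20 or more with an SD of 0.04 to 0.06. Under the step 3 pattern, reaching 2.5% or less needs a gain of about 0.26 at SD 0.06, or 0.34 at SD 0.08.

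**7. What the ratio loses.** Take two replicates: (+0.01 QALY, −300 euros) and (−0.01 QALY, +300 euros). Both ratios are −30,000 euros per QALY. Net monetary benefit (NMB) is threshold × QALY difference − cost difference. At an assumed 25,000 euros per QALY it is 250 + 300 = +550 euros for the first and −250 − 300 = −550 euros for the second.

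**8. Interval behaviour by simulation.** 400 trials of 2,000 replicates were run per scenario, with cost SD 4,000 euros (assumed) and percentile intervals.
- With QALY difference 0.01, SD 0.08 and cost difference 0, replicates split 36% dearer and better, 37% cheaper and better, 15% dearer and worse, and 12% cheaper and worse. The 95% interval for the QALY difference included zero in 87% of trials.
- Coverage of the ratio interval was 0.96 to 1.00 for QALY differences of 0.005 to 0.01. It was about 0.95 when the difference was clear (0.03, SD 0.06).
- NMB intervals from the same replicates covered in about 93% to 96% of trials at thresholds of 0, 20,000, 25,000 and 30,000 euros, in every scenario.

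**The case against.** The strongest reply is that the plan does not rely on this interval alone. The acceptability curve is the share of replicates with positive net benefit at each threshold, so it handles all four quadrants correctly. Costs and QALYs are also compared separately. This stands: a reader who sees both differences is unlikely to mistake a dominated result for a saving. It limits the harm but leaves the interval itself as it is.

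Four stronger readings are tempting and are not supported.

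- *The interval is invalid.* In the simulations its coverage was at or above nominal. The fault is one of interpretation. The article also does not say which bootstrap interval is meant and may leave that to the full plan; the percentile form above is an assumption, although any variant that orders the ratios loses the quadrant in the same way.
- *The QALY difference is bound to be near zero.* The article gives no utility gain, QALY SD or cost figure. That the difference will be small against its SE is an inference. It holds over most of the assumed ranges but not all.
- *The cost per responder has the same fault.* For that ratio the article says only that "The ICER and the 6 months will be subjected to a deterministic and probabilistic sensitivity analysis" and names no confidence interval. At the design effect the denominator is 0.182 with SE √(0.65·0.35/90 + 0.832·0.168/90) = 0.064, so z is about 2.85 and the chance of a negative difference about 0.2%.
- *The interval decides whether the budget impact analysis goes ahead.* The outcomes section makes that analysis depend on the test being cost-effective, but does not tie that judgement to this interval. The cost-utility ratio is listed as a secondary outcome.

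**Conclusion.** The point holds for the cost-utility ratio only, as a matter of interpretability. If the full 18.2-point effect is real, the responder utility gain is 0.10 to 0.20 and the QALY SD is 0.06 to 0.12, about 6% to 35% of replicates would fall on the wrong side of zero. The ratio interval would then mix dominant with dominated results. The conclusion lapses if a large utility gain coincides with a small SD. Because a valid display of uncertainty is already planned, the consequence is one reported interval that is hard to read, not a failed economic analysis.

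**What to change.** For the cost-utility analysis, replace the interval of the ratio by incremental net monetary benefit with a bootstrap 95% confidence interval over a pre-stated range of willingness-to-pay values, computed from the same replicates. Show the cost-effectiveness plane with the share of replicates in each quadrant, beside the acceptability curve already planned. Keep the ratio as a point estimate, and give an interval for it only if practically all replicates have a QALY difference of the same sign.

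The cost is a change of analysis wording; no data or visits are added. The small downside is that results appear for several willingness-to-pay values instead of as one interval.
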